## Analysis

### Statistical considerations

#### Sample size

We aim to have sufficient power to detect a 15% reduction from an estimated 70% that consume antibiotics for the AECOPD during the 4 weeks following randomisation [7]. Trials using CRP testing to reduce antibiotic prescribing for lower respiratory tract infection have resulted in absolute reductions in antibiotic prescribing in the region of 13–22% [32, 38, 39]. Even relatively small changes in prescribing are likely to have beneficial effects on resistance at a population level [16]. Detecting a difference in proportions between 0.70 and 0.55 at the 5% significance level and with 90% power requires a total of 434 participants, inflated to 544 to account for the loss to follow-up of approximately 20% of participants. In addition, we aim to have sufficient power to demonstrate that participants managed with CRP POCT are no worse (non-inferior), compared to those managed without CRP POCT, in terms of their COPD health status measured by the CCQ 2 weeks following randomisation. Assuming an expected difference between groups of zero, a non-inferiority margin of 0.3 lower than the lowest minimal clinically important difference and a common standard deviation of 1.1 [40], based on a one-sided significance level of 0.05 and 90% power, we would need 462 participants, inflated to 580 to account for the loss to follow-up of approximately 20% of participants.

Formulating our overall hypothesis using the Intersection-Union Test [41] we will carry out our individual subhypothesis tests at the 5% level and, if both are significant, conclude overall significance at the 5% level. Power will be affected by the level of correlation between the two outcomes and their respective effect sizes. The impact on overall power is at its greatest when there is zero correlation between outcomes and effect sizes are identical (in this case, the overall power is the product of the powers for testing each individual subhypothesis) [42, 43], and decreases with increasing correlation of outcomes and the more different effect sizes become. We do not expect our effect sizes to be similar, as our co-primary outcomes are two very different constructs (i.e. not two patient-reported outcome measures that are likely to yield similar effect sizes). We also anticipate that the outcomes will not be entirely independent (in those participants who do in fact require antibiotics, antibiotic consumption is likely to be related to COPD health status). We will, therefore, aim to recruit at least 650 participants to maintain an overall power of between 81 and 90%.

### Statistical analysis

Participant characteristics and clinical measures will be summarised using frequencies and percentages, means and standard deviations, or medians and interquartile ranges as appropriate. There will be no planned interim analysis. The assessments made for the internal pilot will be based on recruitment and follow-up rates with no between-group comparison of outcomes. All analyses will be presented as estimates of treatment effects (adjusted mean differences or odds ratios, as appropriate), with associated 95% CIs and *p* values. The main trial analysis will be based primarily on modified intention-to-treat (MITT) population, which will include all randomised participants who provide outcome data, regardless of protocol deviations or intervention received. Missing outcome data will be imputed using multiple imputation in order to obtain a secondary analysis of the primary outcomes based on the full intention-to-treat (ITT) population. A Complier Average Causal Effect (CACE) analysis, that takes into account departures from randomised treatment while maintaining a comparison of groups as randomised, will also be conducted on the primary CCQ analysis [44]. The conclusions drawn on the primary CCQ analysis will be based on both the MITT and CACE analyses. (i.e. the upper limit of the one-sided 95% CI will have to exclude 0.3 in both analyses for non-inferiority to be concluded).

All planned analyses will be described in detail in a Statistical Analysis Plan (SAP), which will be finalised prior to database lock.

### Primary analysis

Our first primary analysis will compare the odds of consuming an antibiotic for an acute exacerbation during the 4 weeks following randomisation, in each trial arm, using logistic regression. Our second primary analysis will compare the mean CCQ score between each trial arm using linear regression, with baseline CCQ scores included as a covariate, and a one-sided 95% CI constructed to assess non-inferiority. We will test if two-level models are required, due to clustering by practice, and fit a single level model if it is not needed. Modelling assumptions will be tested, with appropriate adjustments made in the presence of any violations. Missing primary outcome data are likely to be minimal, but will be accounted for in sensitivity analyses using multiple imputation, where we will assume that primary outcome data are missing at random given observed measurements.

Our second primary analysis, testing the non-inferiority of management with CRP versus no CRP with respect to the CCQ, will be based on our pre-specified margin of 0.3. Should our observed difference be between 0.3 and 0.4 (0.4 is the minimal clinically important difference (MCID) for the outcome), we will consider our results more fully, reflecting on differences found in antibiotic consumption and secondary outcomes (e.g. antibiotic resistance, EQ-5D etc.) in the two trial arms.

Further secondary analyses of the primary outcomes will be conducted:To determine whether any changes in inclusion/exclusion criteria following the internal pilot had any impact on trial findings. The primary analyses will be extended by including an explanatory variable that indicates whether a participant was recruited before or after the change in criteria. The interaction between this variable and trial arm will be included to assess any differential effect this change may have had on the conclusions of the studyModelling antibiotic consumption as repeated observations within individuals using a generalised linear mixed model

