### Randomisation

Participants will be remotely randomised, following consent, using an online computerised randomisation system created by the Centre for Trials Research at Cardiff University. This will be operational 24 h a day. In addition, an 8.30 a.m. to 6.30 p.m. telephone back up will be available if the online system fails or the general practice has problems accessing the online site.

Participants will be randomised in a 1:1 ratio to receive either usual care alone (control) or usual care with the addition of CRP POCT (intervention). Randomisation will use minimisation, with a random element set at 80% to improve the integrity of the randomisation process. Anthonisen criteria (categorised as type 1, 2 or 3) will be used as a minimisation variable, so that balance is achieved with respect to differing levels of COPD exacerbation severity. Remote allocation will maintain allocation concealment from both the participant and the recruiting clinician up to the point of intervention, as this is an open study.

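### Both primary models, as written, leave out Anthonisen type, the factor used for minimisation; adding it is a small, free gain in precision

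*Protocol article*

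**What the plan says.** **Allocation.** The Randomisation section states that "Anthonisen criteria (categorised as type 1, 2 or 3) will be used as a minimisation variable". It names no other factor, so practice is not balanced. Allocation is individual ("Participants will be randomised in a 1:1 ratio") and partly random: "Randomisation will use minimisation, with a random element set at 80" per cent.

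**Primary models.** On antibiotic use, the Primary analysis section says: "Our first primary analysis will compare the odds of consuming an antibiotic for an acute exacerbation during the 4 weeks following randomisation", by logistic regression on arm, with no covariate named. CCQ at 2 weeks is compared "using linear regression, with baseline CCQ scores included as a covariate". On practice it says: "We will test if two-level models are required, due to clustering by practice, and fit a single level model if it is not needed".

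**Elsewhere.** Anthonisen type enters the analysis only in the Subgroup section, as an interaction with arm. The Statistical analysis section speaks in general terms of adjusted estimates, does not say what they are adjusted for, and defers detail to a statistical analysis plan (SAP).

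**The concern.** Minimisation removes most of the chance imbalance between arms on Anthonisen type. If type also predicts the outcome, the treatment estimate varies less from trial to trial than an unadjusted model assumes. The model's standard error is then too large, the confidence interval too wide and the test conservative. Putting the factor in the model restores the match between design and analysis.

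The protocol gives reason to expect that type is prognostic for antibiotic use. The Background says that prescribing recommendations for general practitioners generally rest on symptoms through the Anthonisen criteria, and the Randomisation section treats type as exacerbation severity. At stake is some precision on two co-primary tests that must both succeed. The error is in the safe direction for superiority and for non-inferiority.

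**Working it through.** **1. The plan's own figures.** The Sample size section states: "Detecting a difference in proportions between 0.70 and 0.55 at the 5% significance level and with 90% power requires a total of 434 participants". Allowing for about one-fifth loss, it raises this to 544.

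- Superiority, two-sided 5%, pooled variance, mean rate 0.625: n per arm = [1.960·√(2·0.625·0.375) + 1.2816·√(0.70·0.30 + 0.55·0.45)]² / 0.15² = 216.8, so 217 per arm and 434 in total. This reproduces. 434/0.8 = 542.5; rounding up per arm (217/0.8 = 271.25, so 272) gives the stated 544.
- Non-inferiority, margin 0.3, SD 1.1, one-sided 5%: n per arm = 2·1.1²·(1.645 + 1.2816)² / 0.3² = 230.3, so 231 per arm and 462 in total. This reproduces. 462/0.8 = 577.5, against 580 stated.
- 650 recruited less 20% leaves 520, or 260 per arm. Power is then 94.4% (antibiotics) and 92.9% (CCQ). If the outcomes are independent, overall power is 0.944 × 0.929 = 87.7%, inside the stated 81 to 90%.

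**2. Superiority test: size by hand.** The protocol gives neither the mix of types nor rates by type. Assumed: mix 45/35/20% for types 1/2/3, with control rates averaging about 0.70. With near-perfect balance and no treatment effect, the ratio of true to reported standard error is

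k = √[Σ wₖ·pₖ(1−pₖ) / (0.70·0.30)],

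and the two-sided rejection rate is 2·[1 − Φ(1.96/k)].

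- Mild (0.76/0.69/0.58): Σ = 0.0821 + 0.0749 + 0.0487 = 0.2057; k = 0.990; rejection 4.8%.
- Moderate (0.82/0.67/0.48): Σ = 0.0664 + 0.0774 + 0.0499 = 0.1937; k = 0.960; rejection 4.1%.
- Extreme (0.90/0.63/0.36): Σ = 0.0405 + 0.0816 + 0.0461 = 0.1682; k = 0.895; rejection 2.9%.

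**3. Superiority test: simulation.** 4,000 trials per scenario; 520 evaluable; probability 0.8 of allocation to the balancing arm; logistic Wald test at two-sided 5%; alternative 0.70 against 0.55 overall.

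| Control rates by type | Null rejection, unadjusted / adjusted | Power, unadjusted / adjusted |
|---|---|---|
| None (0.70 throughout) | 4.1% / 4.1% | 94.3% / 94.3% |
| Mild | 4.1% / 4.6% | 94.6% / 95.0% |
| Moderate | 4.3% / 5.4% | 95.7% / 96.4% |
| Extreme | 2.7% / 4.6% | 96.6% / 98.1% |

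The Monte Carlo standard error of a null rejection rate is about 0.3 points. The unadjusted rates in the mild and moderate rows cannot be told apart from the first row, where type does not matter at all. Only the extreme row shows clear conservatism, and it agrees with the hand calculation. The power gain from adjustment is 0 to 1.5 points.

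Unadjusted power does not fall below the no-gradient row. Leaving type out therefore does not breach the planned power; it forgoes a gain.

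**4. CCQ test.** Reported SE = 1.1·√(2/260) = 0.0965. If type explains a share R² of residual variance, the true SE is 0.0965·√(1−R²). One-sided error is 1 − Φ(1.645/√(1−R²)). Unadjusted power is Φ[(0.3 − 1.645·0.0965)/true SE]; adjusted power is Φ(0.3/true SE − 1.645).

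| R² (assumed) | One-sided error, unadjusted | Power, unadjusted / adjusted |
|---|---|---|
| 1% | 4.9% | 93.0% / 93.1% |
| 5% | 4.6% | 93.4% / 93.9% |
| 10% | 4.2% | 93.9% / 94.9% |

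**5. What adjustment does to the odds ratio.** The marginal odds ratio for 0.55 against 0.70 is (0.55/0.45)/(0.70/0.30) = 0.524. In the simulations, the odds ratio within type that gives the same overall 15-point reduction is exp(−0.662) = 0.516, exp(−0.705) = 0.494 and exp(−0.836) = 0.433 for the mild, moderate and extreme gradients. The adjusted figure lies further from 1 because it is conditional on type, not because the intervention does more.

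**6. Practice.** Simulated null rejection when clustering over 70 practices is ignored was 4.7, 4.9, 5.1 and 5.2% at intraclass correlations (ICCs) of 0, 0.05, 0.10 and 0.20. Ignoring practice leaves the test at its nominal level.

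**The case against.** **The SAP may settle it.** The article names no covariate for the logistic model, but it does not say that there is none. It mentions adjusted estimates and defers detail to a SAP that is not shown. This stands in part: nobody can say from the article that the final analysis will omit Anthonisen type. But the Primary analysis section does write the models out, and lists a covariate for one of them. A SAP that follows that text would leave the balancing factor out of both.

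**The size is assumed and small.** This stands. The Background says what recommendations rest on, not how strongly type predicts consumption in practice. A larger gain can be produced: with rates of 88/65/38% by type and a 12-point reduction, power was 84.7% unadjusted and 88.4% adjusted. A reader might infer a loss of 4 points or more from such figures. The documents do not support that as the headline. They give no such gradient, the trial is sized for 15 points, and 12 lies below the 13 to 22% range that the Sample size section cites from earlier trials.

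**The practice rule.** A reader might infer that testing whether practice is needed also makes the superiority test conservative. It does not: allocation is individual, practice is not a minimisation factor, and the level stays nominal (step 6). Nor does the choice move the estimate much. By the usual approximation √(1 + 0.346·variance), with variance = ICC·(π²/3)/(1 − ICC), the practice-conditional and marginal log odds ratios differ by about 1% at an ICC of 0.02 (√(1 + 0.346·0.067) = 1.012) and 3% at 0.05 (√(1 + 0.346·0.173) = 1.030). For CCQ the two mean differences coincide. What remains is that the trial data choose the primary model.

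**Conclusion.** The point holds as a minor one. As written, neither primary model includes the only factor on which allocation is balanced. If that factor is prognostic, both tests are mildly conservative. Superiority null rejection is about 4% under mild to moderate gradients, not clearly different from no effect, and about 2.7% under an extreme one. The power forgone is about 0 to 1.5 points for superiority at the planned 15-point effect, and about 0.1 to 1 point for CCQ if type explains 1 to 10% of residual variance. If type is not prognostic, nothing is lost.

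These sizes assume 520 evaluable participants, a 45/35/20% mix of types, the stated gradients, and the 80% random element read as a probability of 0.8 for the balancing arm. A reading that gives looser balance would make the conservatism weaker.

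The direction and the reading of the text are firm; the magnitudes are not. No false claim of superiority or non-inferiority becomes more likely, and planned power remains inside the stated range.

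**What to change.** In the Primary analysis section, or in the SAP before any comparison by arm, state that both primary models include trial arm and Anthonisen type (three levels) as fixed effects, with baseline CCQ kept in the CCQ model. Add that the adjusted odds ratio is conditional on type and will tend to lie further from 1 than an unadjusted one.

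As a secondary change, replace the test for two-level models with a rule fixed in advance. Either a practice effect or a single-level model would do for the level of the test. If a practice effect is chosen, name the model to use should it fail to converge, still adjusted for type.

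The cost is a sentence or two. Type is already known at randomisation and already needed for the planned subgroup analysis, so no new data are required and the sample size stays as it is.

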### Subgroup

Differential intervention effects on the primary outcomes will be assessed by fitting interaction terms in the primary models between trial arm and the following:COPD severity (Gold grades I/II/III/IV), from most recent spirometry assessmentSeverity of COPD exacerbation (Anthonisen criteria type 1, 2 or 3)Presence of a potentially pathogenic bacteria cultured from sputum sample at baseline

Two exploratory mediation analyses will be conducted using causal modelling techniques to determine whether the effect of the intervention on: (1) antibiotic prescribing and (2) COPD health status is mediated through steroid prescribing.

### Secondary analysis

Secondary outcomes will be analysed in a similar manner to the primary outcomes, with linear, logistic, and Poisson regression models fitted as appropriate.

### Economic evaluation

A within-trial health economic analysis will be undertaken from a health service perspective (UK NHS). Costs due to patient absences from work will also be considered but reported separately. The health economic evaluation will include cost-effectiveness, cost-utility and cost-consequences analyses. A trial-based budget impact analysis will be undertaken to estimate the likely impact of the use of CRP POCT in the management of antibiotic prescribing for COPD on NHS budgets. Prior to commencement of the analysis, a health economic analysis plan will be produced and reviewed by the trial team to be incorporated in the SAP.

Costs will include all resources used in the delivery of CRP POCT. This includes staff training (including travel if relevant), costs of CRP POCT kits and staff time required within the general practices. Resource use through CRP POCT implementation will be estimated through interviews with general practice staff, manufacturers and the trial team. Where additional costs are required (e.g. related to the CRP POCT test), we will obtain them from relevant sources, e.g. manufacturer list prices. Health care resource use (e.g. antibiotic prescribing and consumption, use of other COPD treatments including orally administered steroids primary- and secondary-care consultations, hospitalisations, adverse events) will be collected using data from the in-trial CRFs, participant booklet, the 4-week follow-up questionnaire and an adapted Client Service Receipt Inventory (CSRI) integrated in the 6-month note review to assess the change in profile of health care use as a result of the intervention compared to usual care. Costs will be assigned using published unit costs (e.g. PSSRU, *British National Formulary* (BNF) and NHS reference costs) where available and valued in £ sterling. The health care costs in both the intervention and the control arm will be summated with mean difference per patient in costs (including 95% CIs) calculated for the intervention compared to usual care. As the trial duration is less than 12 months, discounting will not be applied to costs or outcomes.

The primary co-outcomes (assessed at 4 weeks) will be used in the cost-effectiveness analysis. Given that the aim of the trial is whether CRP POCT-informed management of patients with AECOPD can reduce antibiotic use without negatively impacting on recovery, we will consider a range of scenarios. A base-case analysis will report an incremental cost-effectiveness ratio (ICER) presenting the additional cost of producing an extra unit (%) reduction in antibiotic prescribing (expressed as cost per unit % antibiotic prescription avoided). If the main trial fails to demonstrate non-inferiority in terms of the CCQ (as defined above) then the intervention would (if usual conditions apply) likely be regarded as not cost-effective.

We will test a range of scenarios as part of the sensitivity analysis, e.g. best case/worse case scenarios based on the results of the co-primary outcomes to explore the impact on the ICER. A threshold analysis will be undertaken to assess the willingness to accept of the costs of obtaining a reduction in antibiotic prescribing, should the CCQ score fall between the values which will warrant further exploration within the main trial analysis. In addition, we will also explore possible scenarios to reflect subsequent adoption in routine general practice, e.g. exclude the purchase and running costs of the CRP POCT equipment to reflect that the equipment may be used with general practices for a variety of POCT interventions.

We will also undertake a within-trial cost-utility analysis (CUA) to assess the incremental costs per quality-adjusted life year (QALY) gained as a result of the use of CRP POCT compared to usual care at 6 months using the EQ-5D to generate QALYs. QALYs incorporate quantity of life (additional life years) and quality of life in one measure. Thus, by dividing the difference in costs by the difference in QALYs, cost per QALY can be calculated for each comparison.

Generally, the UK National Institute for Health and Care Excellence (NICE) considers an intervention cost-effective if one of the following applies.The intervention is less costly and more clinically effective compared with all other relevant alternatives. In this case, no ICER is calculated as the strategy in question dominates the alternativesThe intervention has an ICER of less than £20,000 per QALY compared to the next best alternative. This means that an investment of up to £20,000 in order to achieve an additional QALY is considered cost-effective

The ICER resulting from the CUA will be compared to the willingness-to-pay threshold of £20,000 per QALY gained as standardised by NICE. No conditions for non-inferiority will be applied in this analysis. Results will be reported as ICERs showing the extra cost of producing one extra QALY or the extra savings achieved by sacrificing one additional QALY.

For both analyses, deterministic sensitivity analysis will be undertaken to assess the extent to which parameter uncertainty affects the ICER. Probabilistic sensitivity analyses will be run to estimate the probability of the ICER falling below a range of willingness-to-pay (or accept) thresholds as standardised by NICE. For the cost-effectiveness analysis, no such threshold exists, thus we will examine the academic literature and opinions from the clinical team on what would constitute a suitable willingness to pay.

A cost-consequence analysis will present all relevant primary and secondary outcomes alongside the costs in tabular form (without combining them into ICERs) to leave decision-makers the option to form their own view of relative importance.

A trial-based budget impact analysis (BIA) will be undertaken to estimate the likely impact of the use of CRP POCT on NHS budgets through implementation costs, changes in health care usage and potential reduction of antimicrobial resistance. The BIA will be based on the size and composition of the trial population and informed by trial data supplemented by the best available published evidence where required. Sensitivity analyses will be undertaken to estimate the range of a potential budget impact considering parameter uncertainty.

